**Theoretical results**

- Confirmation of the hypothesis that maternal vitamin D supplementation at a dose of 1200 IU/d is more efficient than 400 IU/d for lactating women, and safe for both mother and child, and positively changes bone mass and body composition (better ratio between muscle and fat components)
- Verification of a maternal need for vitamin D supplementation during lactation and modification of current recommendations
- Confirmation of the effectiveness of vitamin D supplementation at the currently recommended dose in breastfed infants
- Confirmation of the hypothesis that the season of delivery has an influence on maternal and newborn vitamin D status, and if so, a change in the currently recommended vitamin D supplementation according to season.

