**Introduction**

Lactating women and their offspring are at risk of vitamin D deficiency. Vitamin D supplementation at a dose of 400 IU/d is not sufficient for lactating women, and higher doses are required (up to 2000 IU/d). Vitamin D supplementation at a dose of 4000-6000 IU/d during lactation was safe for both lactating women and their offspring. However, the safety of such high doses has only been proved in studies with a small number of participants. The safety and effectiveness of vitamin D supplementation at doses higher than 400 IU/d have not yet been studied in Polish lactating women. A high incidence of vitamin D deficiency in pregnant and lactating women and their offspring has been reported. An appropriate vitamin D intake is a fundamental issue because of the role of vitamin D, not only in calcium and bone homeostasis, but also in many other physiological functions. Vitamin D may have an influence on the musculoskeletal system (body composition parameters and interactions between them).

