**Aim of the study**

We aim to prospectively compare the influence of vitamin D supplementation (400 IU/d vs. 1200 IU/d) on the vitamin D status, bone mass and body composition of lactating women and their offspring, taking safety issues into account. Additionally, we want to prove that vitamin D supplementation at a dose of 400 IU/d is sufficient to build up an appropriate vitamin D status in breastfed infants, irrespective of maternal vitamin D supplementation (up to 1200 IU/d). We also aim to assess the influence of the season of delivery on the maternal and newborn’s vitamin D status.

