**Patients**

150 lactating mother-infant pairs.

*Inclusion criteria*

Healthy women, declaring breastfeeding for 6 months.

Breastfed term newborns without major medical problems.

*Exclusion criteria*

Maternal diabetes, maternal endocrine disorders during pregnancy, multiple gestation.

Liver diseases and cholestasis, renal insufficiency, endocrine disorders, congenital malformations and anticonvulsant treatment in neonates.

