**Methods**

This is a prospective double-blind randomized control trial. Intervention in mothers will last for 6 months. Lactating mothers will be randomly allocated to two groups with different vitamin D intakes.

Group 1 – Maternal vitamin D supplementation at a dose of 400 IU/d (multivitamin tablet containing 400 IU of cholecalciferol + placebo),

Grupa 2 – Maternal vitamin D supplementation at a dose of 1200 IU/d (multivitamin tablet containing 400 IU of cholecalciferol + 800 IU of cholecalciferol),

All infants will receive 400 IU/d of vitamin D3 (1 capsule or 1 drop) throughout breastfeeding, according to the Polish recommendation.

The following assessments are planned during the study:

- Maternal and infants’ data (gestational age, birth weight, Apgar score, vitamin D intake from diet and supplements, educational/socioeconomic status, duration of sunlight exposure, usage of sun blockers)
- Anthropometric measurements (weight, height/length, maternal BMI)
- Assessment of vitamin D status (measurement of serum 25 hydroxyvitamin D (25-OHD) and serum parathormone (PTH))
- Assessment of biochemical signs of vitamin D overload (serum calcium, urinary calcium and creatinine (urinary calcium /creatinine ratio)).
- Assessment of bone status (total body and lumbar spine bone mineral content (TB BMC L1-L4 BMC), total body and lumbar spine bone mineral density (TB BMD, L1-L4 BMD) by dual energy X-ray absorptiometry
- Assessment of body composition (lean body mass (LBM) and fat mass (FM)) by dual energy X-ray absorptiometry
- Statistical analysis (distribution analysis, Student’s T test for normally and U-Mann-Whitney test for non-normally distributed variables, chi^2^ test for categorical variables, Pearson or Spearman correlation, one-way analysis of variance or Friedman ANOVA test). *P*-values <0.05 were considered significant.

*Schedule of study visit*

Baseline assessment (before introduction of vitamin D supplementation) will provide baseline characteristics of the studied participants. Cord blood samples will be collected at delivery. Maternal baseline blood samples will be collected within 3 weeks after delivery when maternal and infants’ DXA measurements will be performed. Follow–up visits will take place at the 3^rd^ and 6^th^ month after delivery.

Biochemical measurements in serum will be performed by fully automatic methods to minimize collected blood volume at 2ml.

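### The protocol expects to confirm that 1200 IU/d is safe for mother and child, but its size, two biochemical markers and difference tests without a margin cannot confirm that

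*Protocol*

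**What the plan says.** The Theoretical results section of the protocol lists, as one hypothesis to be confirmed, that 1200 IU/d works better than 400 IU/d in lactating women and is "safe for both mother and child, and positively changes bone mass and body composition". The same list anticipates that current recommendations may be modified. The Aim mentions safety only in passing: "taking safety issues into account".

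The means for reaching that conclusion are in Patients and Methods:

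- Size: "150 lactating mother-infant pairs".
- Design: "Lactating mothers will be randomly allocated to two groups with different vitamin D intakes". No allocation ratio is given.
- Duration: "Intervention in mothers will last for 6 months".
- Safety measures: "Assessment of biochemical signs of vitamin D overload", namely serum calcium and urinary calcium relative to creatinine.
- Group comparisons: "T test for normally and U-Mann-Whitney test for non-normally distributed variables", with chi-square for categorical variables and significance at P<0.05.

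The protocol gives no limit for an abnormal value, no acceptable event rate, no margin for a safety comparison, and no power or dropout assumption.

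**The concern.** The efficacy half of the hypothesis can be confirmed by rejecting a null hypothesis of no difference. The safety half cannot, because the listed tests can show that a difference exists but not that harm is absent or acceptably rare. Without a margin or an acceptable rate, a reader of the results is likely to take a non-significant comparison as the promised confirmation. A smaller or more depleted trial would reach that result more easily.

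The wording is also broader than the data. It claims general safety for two populations, mothers and infants, on the strength of two biochemical markers observed for 6 months. Because the protocol links its expected results to a change in recommendations, an overstated safety conclusion could carry weight beyond the trial.

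**Working it through.** **Reproducing the plan's figure.** The 150 pairs cannot be reproduced, because the protocol gives no effect size, event rate, standard deviation, margin, power or dropout. What can be checked is how much information that size carries on safety.

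**Inputs.** From the protocol: 150 pairs, two arms, significance level 0.05. Assumed: 1:1 allocation, so 150/2 = 75 per arm; two-sided testing; 60 or 50 evaluable per arm to show the effect of losses; and all event rates below, which are illustrative.

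**1. Upper limit when no event is seen on 1200 IU/d.** The exact two-sided 95% upper limit for 0/n is 1 − 0.025^(1/n).

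- n = 75: 1 − 0.025^(1/75) = 4.80%
- n = 60: 1 − 0.025^(1/60) = 5.96%
- n = 50: 1 − 0.025^(1/50) = 7.11%

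**2. Upper limit when events do occur.** For x events the Clopper-Pearson upper limit is the 97.5% quantile of a Beta(x+1, n−x) distribution. With n = 75 it is 7.2% for one event, 9.3% for two and 11.2% for three. With 2/60 it is 11.5%.

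**3. Chance of seeing no event at all, (1 − p)^n.** With 75 on the higher dose:

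- true rate 1%: 0.99^75 = 0.471
- true rate 2%: 0.98^75 = 0.220

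So a clean sheet is quite possible with a real rate of 1% or 2%. Conversely, at a true rate of 2% the 4.8% limit would be obtained only about one time in five.

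**4. Power of the listed chi-square test.** This is the sum, over all pairs of event counts, of the product of the two binomial probabilities wherever the uncorrected chi-square exceeds 3.84, with 75 per arm.

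| Assumed rates (400 vs 1200 IU/d) | Power |
|---|---|
| 2% vs 4% | 9% |
| 5% vs 10% | 22% |
| 2% vs 8% | 40% |
| 10% vs 20% | 41% |
| 2% vs 10% | 57% |
| 5% vs 20% | 83% |
| 2% vs 15% | 88% |

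With 60 per arm, 2% vs 8% falls to 31%. A doubling at any of these base rates, or a rise from 2% to 8%, would more often than not be non-significant. Rises of 13 to 15 percentage points would probably be detected.

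**5. Comparison of means.** The difference detectable with 80% power is (1.96 + 0.84) × √(2/75) = 0.46 SD. Power is 86% for a 0.5 SD shift and 45% for 0.3 SD.

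**6. What a formal safety comparison would need.** For non-inferiority on a binary event with equal true rates, one-sided 0.025 and 80% power, the number per arm is (1.96 + 0.84)² × 2p(1 − p)/margin². This gives 124 for p = 2% with a margin of 5 points, 299 for 5% with 5 points, and 75 for 5% with 10 points. The present size therefore matches only a wide margin, before any loss.

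**The case against.** The strongest reply has five parts.

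- Theoretical results is a list of hoped-for outcomes, not an endpoint or decision rule. This is true and limits the severity. Even so, it is where the protocol states what it expects to conclude, and the word used there is too strong.
- The Methods list tests by type of variable and assign none to the calcium measures. This stands. A reader might infer that safety will be judged by comparing average calcium, so that a few abnormal individuals are missed. The protocol does not say so, and the listed chi-square test is compatible with counting participants above a limit. The point does not depend on that inference, since every between-group test listed is a test for difference.
- Laboratory limits and summary tables commonly belong in an analysis plan. This also stands, and their absence here is not the fault. No analysis plan, however, can turn these numbers and difference tests without a margin into confirmation of general safety.
- The trial is not blind to harm. A large rise in abnormal values, or a shift of about half a standard deviation in the mean, would probably be detected. It would therefore be wrong to say that safety would be concluded almost by default.
- A reader might infer that the Introduction contradicts this design, because it remarks that "the safety of such high doses has only been proved in studies with a small number of participants". That sentence concerns 4000-6000 IU/d, not 1200 IU/d. It is not a contradiction and is not used as support here.

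**Conclusion.** The concern holds in a limited form. As written, the protocol can describe biochemical tolerability over 6 months and can probably detect large harmful effects. It cannot confirm that 1200 IU/d is safe for mother and child, because non-significance at this size is compatible with a doubling of the event rate, or with a rise from 2% to 8%. Power for the assumed contrasts 2% vs 4%, 5% vs 10% and 2% vs 8% is 9%, 22% and 40%. The best attainable exact two-sided 95% upper limit on an event rate is 4.8%, and only with zero events in 75 evaluable pairs.

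These figures rest on 1:1 allocation, no losses, two-sided testing and illustrative event rates, none of which the protocol states. Losses would make the position worse. It would be a mistake to state flatly that the trial excludes rates above about 5%: one event in 75 already moves the limit to 7.2%. Nothing here bears on which dose is appropriate.

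**What to change.** 1. In Theoretical results, replace the claim of safety with a conclusion limited to biochemical signs of vitamin D overload in mothers and infants over 6 months.
2. Report per arm, for mothers and infants separately, the number and proportion with serum calcium or urinary calcium/creatinine above a pre-stated laboratory limit, with exact 95% confidence intervals, and the risk difference between arms with its 95% confidence interval. The limits and the event definition can sit in the analysis plan.
3. State that a non-significant difference will not be read as evidence of safety.
4. State the attainable precision conditionally: with zero events the two-sided 95% upper limit is 4.8% for 75 evaluable pairs and 6.0% for 60; in 75 it is 7.2% with one event and 9.3% with two.

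The cost is a few sentences and one extra table, with no added participants, samples or visits. The downside is a less favourable safety claim.

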**Benefits for patients**

This study will help to optimize prophylactic strategies against vitamin D deficiency in lactating women and their offspring, and also protect against the long-term medical consequences of vitamin D deficiency. It is well-known that vitamin D deficiency increases the risk of osteoporosis, autoimmunological diseases, cancers and cardio-vascular diseases. This study may improve the quality of women’s and children’s lives in the future.
